   2. **Aims:** This prospective study aims (1) to design an image-based VR (IBVR) instruction for clinical medical education, (2) to compare HRV and CL in traditional video-based (VB) learning and novel IBVR-based learning, (3) to compare outcomes of mini-CEX, DOPS, and milestone between two modules, (4) to perform a qualitative evaluation of IBVR-based learning using a 360-degree video review, and (5) to assess various levels of novice learners (undergraduate medical students and postgraduate year residents) for their participation in and acceptance of this novel IBVR-based learning.
   3. **Study Designs:** This 3-year study includes two parts: (1) Design a VR-based curriculum including fundamental otolaryngological skills, and (2) Validation of an IBVR-based history taking and physical examination (H&P) learning activity using a blinded randomized, parallel-controlled trial in convenience-sampled novice undergraduate medical students and postgraduate year residents.
   4. **Materials and Methods:** This study will be implemented between August 1, 2017 and July 31, 2020. Firstly, a VR-based curriculum will be designed including H&P using the analysis, design, development, implementation, and evaluation model and a modified Delphi approach. VB module and IBVR module of the same contexts will be developed. Secondly, an IBVR-based H&P learning activity will be validated by measuring CL questionnaires, reaction time, HRV, mini-CEX, DOPS, milestones, global satisfaction scale and AttrakDiff2 questionnaires (n = 64). Age, sex, and cognitive style (determined by the Group Embedded Figures Test) of both groups are matched. Differences in variables of interests will be statistically analyzed.
2. **Study Design**
   1. **Study Type:** Interventional (Clinical Trial)
   2. **Actual Enrollment:** 64 participants
   3. **Allocation:** Randomized
   4. **Intervention Model:** Parallel Assignment
   5. **Intervention Model Description:** This randomized controlled trial will recruit 64 subjects who are novices in otolaryngology at an academic teaching hospital. The cognitive style of the participants is assessed using the Group Embedded Figures Test. The subjects are randomly assigned (1:1) to a novel image-based virtual reality group and conventional video-based group matched by age, sex, and cognitive style.
   6. **Masking:** Double (Investigator, Outcomes Assessor)

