In the ***second-year study***, we will perform a prospective, randomized, controlled, crossover trial to validate the efficacy of IBVR-based surgical trainings in otolaryngological novice residents (R1 & R2) in the operation room. Because we trained 5–6 new residents in each year at our department (total 10–12 junior residents at Linkou–, Keelung–, and Taipei– Chang Gung Memorial Hospital), we need to use a crossover study design (sample size = 10). A crossover study is a longitudinal study in which subjects receive a sequence of different interventions in many scientific disciplines, for example psychology, education, pharmaceutical science, and medicine. Randomized, controlled crossover experiments are especially important in health care. A crossover clinical trial is a repeated measures design in which each participant is assigned to a sequence of interventions, including at least two modules. Two of our learning objectives in surgical trainings are “The residents can precisely and proficiently prepare pre-operative setup of complex surgeries” and ‘The learners can precisely and proficiently perform basic surgeries.’. Each session of 15-minute VB or IBVR-based instruction with monitoring HRV are randomly allocated to the participants before operation. Reaction time and CL questionnaires are immediately tested after learning. Then the residents will perform a formal operation with video recording using a 360-degree digital camera for 15 minutes. The teachers are blinded to VB/IBVR information need to carefully assess the prevision and proficiency of operation, communicational skills, nurse-doctor relationship, etc., using the DOPS and milestone instruments, and prevent the patients from potential harm. Then the residents can watch their own IBVR video and find their deficiency and immediately discuss with the teachers (bidirectional feedbacks). The participants need to provide their reflection in their feedbacks. They will receive the same module of 4 consecutive sessions then receive the other module subsequently. The interval between VB and IBVR of the same operation is at least 1 month (wash-out period) to minimize possible overlapping training effects.

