In the ***third-year study***, the participants will complete 4 sessions of VB or IBVR surgical trainings and then switch to receive IBVR or VB surgical trainings. Finally, the participants will complete 8 sessions of basic surgical training with 2 different modules, and they will rate their GSS and learning experience. At the end of this study, group interviews will be performed to gather their feedbacks and reflections. The investigators can also qualitatively evaluate this IBVR-based surgical trainings.

1. **Null Hypothesis:**
2. DOPS and milestone scores of IBVR learning are equivalent to those of VB learning.
3.
[figure not shown]
CL in terms of CLS, TLX, CLL, and reaction time of IBVR learning are equivalent to those of VB learning.
4. Stress in terms of HRV of IBVR learning are equivalent to those of VB learning.
5. Satisfaction and learning experience of IBVR learning are equivalent to those of VB learning.
6. **Participants**

The **inclusion criteria** of the present study are:

1. Age > 20 years old;
2. Junior residents (R1 and R2).

The **exclusion criteria** are:

1. Pregnant, hypertension, recent motion sickness, inner ear infections or claustrophobia, recent surgery, pre-existing binocular vision abnormalities, heart conditions or epileptic symptoms;
2. Declining to participate.
3. **GEFT (15 minute):**

We plan to recruit 10 volunteers from 12 junior residents who have listened our initial instruction of the present study and completed a 15-minute GEFT.^54^ We will apply an English version of the GEFT that GEFT scores ≤12 are considered as ‘FD’ and those with GEFT scores >12 are regarded as ‘FI’.

1. **Randomization:**

The randomization procedure assures balanced design in age, gender, and FD/FI. Computer-generated lists of random numbers are created using Random Number Generators of SPSS software for allocation of the participants and are stratified by center with a 1:1 allocation (Rv. Uniform [0, 1]). The allocation sequence is concealed from the blinded researcher before instruction adhering to our computer-generated randomization protocol. Participants are randomly allocated to either IM or PPS group. Half of the patients are randomized to the IBVR group and the remaining patients are randomized to the VB group. This protocol follows the rules of the CONORT 2010.^58^

1. **Learning Material Provided (15 minutes):**

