GSS and AttrakDiff2 are assessed at the end of each session and at the end of the third study. Each sessional GSS and learning experience can help us to improve our quality of instructional design. Overall GSS, PQ, HQ-S, HQ-I, and ATT can help us to understand the reasons of product acceptance. Such information will help us to make further progresses in instructional design of IBVR-based learning.

1. **Outcome Measurements and Statistics:**

Primary outcome is DOPS score. Because of longitudinal, crossover, repeated measures design of the present study, we use the generalized estimating equation (GEE) approach with mixed models that include random effects to facilitate analysis of data. Differences in scores of DOPS, milestones, CLS, TLX, CLL, GSS, PQ, HQ-S, HQ-I, and ATT, changes in reaction time and HRV, and % of change in reaction time and HRV are compared using the GEE test.

1. **Statistical Analysis:**

Data are analyzed using the SPSS 23.0 software (SPSS Inc., an IBM company, Chicago, IL, USA) and GraphPad Prism 5 software (GraphPad Software, Inc., San Diego, CA, USA). Statistical significance will be determined using the Mann-Whitney *U* test, Wilcoxon rank test, chi-square test, or the Fisher’s exact test as appropriate. Besides, content validity index (content validation of both VB and IBVR modules) and Cronbach’s alpha (internal consistency) will also be calculated. Correlation between variables of interests were analyzed using Spearman’s rank correlation coefficient. Besides, two-way analysis of variance (ANOVA) is used for examining the influence of two different categorical independent variables (male/female & VR-based modules; FD/FI & VR-based modules; high/low CL & VR-based modules; high/low stress & VR-based modules) on learning outcome measurements. Two-sided *P* values < 0.05 are considered statistically significant.

1. **Anticipated possible problems and resolutions**

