2. We may need more eligible candidates as anticipated since we want to control age, gender, and FD/FI ratios. Fortunately, there are approximate 100 UME and PGY students from various medical colleges to be trained in our Teaching Clinics each year. Moreover, participants may withdraw from the trial or become "lost to follow-up" in most longitudinal studies of human subjects. According to our previous experience, we extremely need an experienced research assistant (RA) to recruit subjects, obtain written inform consent forms, performing experiments, and manage our experimental data. The best resolution is the MOST agree us to hide a RA in this three-year study.
3. Such as mentioned above, missing-data will be a big problem in this longitudinal study. In additional to a full-time RA, we can use an optimal method such as GEE approach to analyze the data according to the principle of the intention to treat.
4. Despite we have some experience in instructional design of mobile e-learning (M-TEL), VR is still a tremendous challenge to us because of complex program and hardware technologies and expensive instruments. Due to limited resource, we construct an experienced team including experts of medical education.
5. **Anticipated Outcomes:**
   1. **Anticipated progression of the study**

We will conduct the three-year study between August 1, 2017 and July 30, 2020. In the first year, we plan to design a VR-based curriculum including H&P and parts of basic surgeries with verification in a pilot study and validate an IBVR-based H&P learning activity using a blinded randomized, parallel-controlled trial in convenience-sampled novice UME and PGY learners (*n* = 24). In the second year, we will complete the design work of a VR-based surgical trainings with verification in a pilot study and finish the validation of an IBVR-based H&P learning activity using a randomized controlled trial (*n* = 40), and begin to recruit 10 junior residents to validate a basic IBVR-based surgical trainings using a randomized, controlled, crossover trial in convenience-sampled novice residents. In the third year, we will complete the validation of IBVR-based surgical trainings using a randomized crossover trial, and data analysis and manuscript preparation.

- 1. **Anticipated contributions to academic research, national development, and other clinical applications**

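### If the crossover part is still in the study, its stated analysis merges two model classes and, run as an ordinary GEE on 10 residents, does not hold the two-sided 5% level; no period term is named

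*Protocol*

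**What the plan says.** The crossover is described in the Detailed Protocol, section 4 (Materials and Methods), under the validation of basic IBVR-based surgical trainings. Its size comes from the number of residents available: "we need to use a crossover study design (sample size = 10"), and under GEFT, "We plan to recruit 10 volunteers from 12 junior residents". The order of modules is randomized 1:1 with half in each group. On the sessions: "They will receive the same module of 4 consecutive sessions then receive the other module subsequently". The same operation is taught by both modules, at least one month apart.

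Under Outcome Measurements and Statistics for this part, the primary outcome is DOPS, and "we use the generalized estimating equation (GEE) approach with mixed models that include random effects". The next sentence says the outcomes "are compared using the GEE test". The Statistical Analysis paragraph adds that two-sided P "values < 0.05 are considered statistically significant". No period term, sequence term or small-sample correction is mentioned.

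The Protocol is not consistent on whether this part is still planned. The synopsis (Study Designs) says "This 3-year study includes two parts", namely curriculum design and the parallel history-and-examination trial. Section 4 (Study design) introduces the three-part plan with the word originally. Yet the Objectives still include basic surgery and junior residents, the crossover keeps its own hypotheses, eligibility, randomization and statistics, and the year plan still says the team will "begin to recruit 10 junior residents to validate a basic IBVR-based surgical trainings using a randomized, controlled, crossover trial".

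**The concern.** There are two separate faults.

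The first is that the method is not defined. A GEE estimates a population-average effect, with a working correlation and a robust variance. A mixed model estimates fixed effects conditional on random effects, by likelihood. Two analysts could follow the sentence in good faith and report different standard errors and P values. The choice also matters for missing data, which the section on anticipated problems calls a big problem and proposes to handle by GEE: ordinary unweighted GEE needs a stronger missing-data assumption than a likelihood-based mixed model. If the GEE label is taken at face value, 10 clusters are too few for the usual robust standard error with a normal reference, and the stated 0.05 is not the error rate obtained.

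The second is period. Every resident meets the same operations again in the second block. Novice surgeons are expected to improve with repetition, and a one-month gap does not undo a learned skill. If the model has no term for period, that improvement goes into the residual variation, and with unequal sequences it also enters the module estimate.

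**Working it through.** **Inputs from the Protocol.** 10 residents; two blocks of 4 sessions, one module per block; half of the residents in each order; two-sided 0.05. The figure of 10 has no effect size, power or formula behind it, so there is no calculation to reproduce.

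**Assumptions not in the Protocol.**
- Within-resident differences are normal.
- Their SD is 5 points, range 3.5 to 7. The value 5 follows from a session SD of 10 (borrowed from the parallel part's pilot, 85±10 and 90±10), an assumed within-resident correlation of 0.5 and 4 sessions per module: variance = 2 × 10² × (1 − 0.5) / 4 = 25.
- The module effect is 5 points, the same pilot difference.
- Learning between periods is 0, 2.5, 5 or 10 points.

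**Step 1: error rate without a period term.** In this balanced layout the GEE estimate is the mean of the 10 within-resident differences. The uncorrected robust variance divides by N rather than N − 1, so z = t × √(N/(N − 1)) with t on 9 df. Rejecting at |z| > 1.96 means |t| > 1.96 × √(9/10) = 1.859.

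Type I error = P(|t₉| > 1.859) = 9.6%. A fitted exchangeable GEE in 1,500 simulated trials gave 8.7%.

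**Step 2: error rate with a period term, 5:5 split.** Two means are now estimated, leaving 8 df: |t| > 1.96 × √(8/10) = 1.753.

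Type I error = P(|t₈| > 1.753) = 11.8%. The fitted GEE gave 11.3%.

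Neither exact figure depends on the DOPS SD.

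**Step 3: bias from learning without a period term.** Let τ be the module effect and L the learning effect. The difference IBVR minus VB has mean τ + L when IBVR comes second and τ − L when it comes first. The average over residents is τ + L × (n₂ − n₁)/N, where n₂ and n₁ are the numbers with IBVR second and first.

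| Split | Bias (absolute) | With L = 5 | With L = 10 |
|---|---|---|---|
| 5:5 | 0 | 0 | 0 |
| 6:4 | 0.2 L | 1 point | 2 points |
| 7:3 | 0.4 L | 2 points | 4 points |

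**Step 4: error rate and power, 5:5 split, SD of differences 5.** Learning adds a between-sequence spread of ±L to the differences, which the test without a period term treats as noise.

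| Learning (points) | Type I error, GEE, no period | Power for 5 points, GEE, no period | Power, period term and t on 8 df |
|---|---|---|---|
| 0 | 9.6% | 89% | 79% |
| 2.5 | 6.4% | about 84% | 79% |
| 5 | 1.9% | about 68% | 79% |
| 10 | 0.02% | about 16% | 79% |

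The last column has type I error 5.0% at every learning size. The 89% in the first row is not a fair benchmark, because that test runs at 9.6%.

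With an SD of differences of 7, GEE power without a period term falls from 66% to 50% (L = 5) and 18% (L = 10), and the period-adjusted t test has 51%. With an SD of 3.5, the corresponding figures are 99%, 85% and 12%, and the t test has 98%.

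**The case against.** The strongest reply is that this part may no longer exist. The word originally in section 4, the two-part synopsis, and the 64 participants and outcomes listed at the front all point that way, and the synopsis aims mention neither surgery nor junior residents. That stands as a reason to make the point conditional. It does not dispose of it, because no passage withdraws the crossover and the later sections still plan it in full.

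The second reply is that period terms, small-sample corrections and the reference distribution are often left to a statistical analysis plan, which is not shown here. This also stands in part. The Protocol is silent on period; it does not exclude it. It does not prescribe an uncorrected robust error either, so 9.6% and 11.8% describe the usual default and not something the text orders. What the Protocol does fix, and fixes badly, is a sentence that joins two incompatible model classes.

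A reader might infer that the analysis cannot be carried out. That is too strong: either a GEE or a mixed model can be fitted, and the text simply does not say which.

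A reader might also infer that the missing period term inflates the error rate. It does not. With 5:5 sequences, omitting it makes the test conservative once learning is appreciable (1.9% at 5 points), and adding it to an uncorrected GEE raises the error to 11.8%. The inflation comes from having few clusters.

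Nor does learning bias the module effect under the stated half-and-half allocation. Bias needs an imbalance. Withdrawals alone cannot turn 5:5 into 7:3; losing two residents from one order gives 5:3, a factor of 2/8 = 0.25. A 7:3 split would need the allocation itself to depart from half and half. This part states no block size, unlike the parallel part, which uses blocks of 4.

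**Conclusion.** The point holds conditionally. If the crossover remains, its stated analysis contradicts itself. Read as the named GEE with the usual robust Wald test, it runs at about 9.6% instead of 5% (no learning, normal differences), or about 11.8% with a period term and no small-sample correction at a 5:5 split.

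The unmentioned period term is a separate weakness. With balanced sequences it costs power, potentially most of it, without bias. With unequal sequences it biases the module effect in proportion to the imbalance. The bias factors are plain arithmetic. The power figures rest on an assumed SD of differences and assumed learning effects, and should be read as showing direction and rough scale.

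It would be wrong to conclude that the main trial is compromised. The 64-participant parallel comparison has its own analysis, and nothing here touches it.

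**What to change.** First reconcile the synopsis, the Objectives, section 4 and the year plan on whether the crossover is still part of the study.

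If it is, replace the GEE-with-random-effects sentence, and the GEE test that follows it, with one method. Either of these would serve:
- a linear mixed model with fixed effects for module, period, sequence and operation, a random resident effect, and Satterthwaite or Kenward-Roger degrees of freedom;
- a period-adjusted t comparison of within-resident differences between the two sequences.

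State that the module effect assumes no differential carry-over of learning. A period term alone is not enough; the small-sample reference must come with it.

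If the crossover has been dropped, delete it from the objectives, hypotheses, statistics and year plan.

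Either way the change is to wording only and needs no extra residents. The cost is wider confidence intervals than an uncorrected GEE would report, and, where there is no learning, lower apparent power (79% against a nominal 89% under the assumptions above).

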In the ***second-year study***, we will perform a blinded randomized, parallel-controlled trial to validate the efficacy of IBVR-based learning activity among multilevel otolaryngological novice learners for H&P training at the ‘Teaching Clinics”. One of our learning objectives in Teaching Clinics is ‘The learners can precisely and proficiently perform H&P in outpatients.’. There are 4 steps in Teaching Clinics: 1) debriefing, 2) H&P, 3) assessment, and 4) feedback. VB or IBVR-based teaching for 10 minutes with monitoring HRV and immediate assessment of CL questionnaires and reaction time are implemented before receiving information and situation-based reminders of context in the first step. The participants will be randomly allocated to use a VB module or a IBVR module under the control of age, sex, and FD/FI. Then the leaners will perform H&P with video recording using a 360-degree digital camera for 10 minutes. The teachers are blinded to VB/IBVR information and need to carefully assess the prevision and proficiency of H&P, communicational skills, patient-doctor relationship…, etc. using the mini-CEX, DOPS, and milestone instruments, and prevent the patients from potential harm. Then the learners can watch their own IBVR video and feedback to and discuss with the teachers (bidirectional feedback) and provide their reflection whereas the investigators can qualitatively evaluate this IBVR-based H&P learning activity. Finally, the learners will rate their GSS and learning experience.

1. **Null Hypothesis:**
2. Mini-CEX, DOPS, and milestones scores of IBVR learning are equivalent to those of VB learning.
3. CL in terms of CLS, TLX, CLL, and reaction time of IBVR learning are equivalent to those of VB learning.
4. Stress in terms of HRV of IBVR learning are equivalent to those of VB learning.
5. Satisfaction and learning experience of IBVR learning are equivalent to those of VB learning.
6. **Participants**

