Primary outcome is score of DOPS. Differences in scores of mini-CEX, DOPS, milestones, CLS, TLX, CLL, GSS, PQ, HQ-S, HQ-I, and ATT between IBVR module and VB module are compared using Mann-Whitney *U* test. Changes in reaction time and HRV between IBVR module and VB module are compared using Wilcoxon rank test. Percentage (%) of change ([intervention value – baseline value]/[baseline value] × 100) in reaction time as well as HRV will be calculated and compared with Mann-Whitney *U* test or Wilcoxon rank test as appropriate.

1. **Validation of basic IBVR-based surgical trainings using a randomized, controlled, crossover trial in convenience-sampled novice residents**

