As mentioned above, there is widespread concern regarding the inadequacy of otolaryngological teaching at novice level. Improvement in M-TEL and VR-based learning of otolaryngology can drive improved learning outside the classroom. New, additional methods of teaching covering a range of 6-core competencies will be shown to be valid and reliable. Thorough medical curricula should include classroom lectures, M-TEL learning, VR simulation, clinical placement, and assessment in order to enhance otolaryngological knowledge and clinical skills for novice learners according to CL theory. This study will design an economic, feasible, safe IBVR-based instruction for self-directed learning and enhancement of self-efficacy. Moreover, identification of personally cognitive style and copping style to stress and/or CL overload can help the learners to choose a proper instructional material on the VR-based instructional system. This novel IBVR-based instruction can reform the otolaryngological learnings in novice learners. Finally, the novices can better their performance in fundamental otolaryngological skills without significant increasing their CL and stress, and ultimately improve patient safety.

- 1. **Anticipation of trainings for study researchers**

The medical teachers can be familiar with the design of the IBVR-based instruction and increase their ability of handling VR-based learning to effectively blend instructional design, CL theory, and learning objective principles. The professors of VR/AR instruction can extend research to medical education in novice level. The computer programmers can train their ability to establish an innovative IBVR-based learning tool to deliver medical education. Finally, we can combine traditional cognitive theory, learning principles, and psychophysiology in the design of new VR-based instruction.

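### The anticipated no-increase conclusion on cognitive load and stress has no interval or margin behind it, and a non-significant difference test at 32 per arm could not support it

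*Protocol*

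**What the plan says.** In the parallel-trial section of the Protocol, under Null Hypothesis, the load hypothesis reads "CL in terms of CLS, TLX, CLL, and reaction time of IBVR learning are equivalent to those of VB learning" and the stress hypothesis reads "Stress in terms of HRV of IBVR learning are equivalent to those of VB learning". (CLL is taken here to mean the CLC questionnaire.) The crossover section repeats both.

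Under Outcome Measurements and Statistics for the parallel trial, the questionnaire scores "between IBVR module and VB module are compared using Mann-Whitney *U* test". For the other two measures, "Changes in reaction time and HRV between IBVR module and VB module are compared using Wilcoxon rank test". The Statistical Analysis section gives one criterion: "Two-sided *P* values < 0.05 are considered statistically significant". Neither section states a margin or a confidence-interval rule for load or stress.

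The section on anticipated contributions then expects that "the novices can better their performance in fundamental otolaryngological skills without significant increasing their CL and stress, and ultimately improve patient safety".

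The Virtual Reality section of the introduction reports earlier work by the same team. There, changes in a multiple-choice test of 155% ± 126% and 56% ± 54% (P = 0.303) are called equivalent.

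**The concern.** A two-sided difference test can show that load or stress differs between modules. It cannot show that they are the same, or that one is no higher than the other. If a non-significant result is taken as no increase, the claim gets easier to make as the data get less precise.

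The wording invites that step: the nulls are called equivalence, failing to reject them leaves equivalence standing, and the anticipated conclusion speaks of no significant increase. The introduction shows the step already taken once, with two means 99 percentage points apart (155 − 56).

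The outcome matters here. Load and HRV are in the official title, and comparing them is the second aim. The section on VR, CL and medical education says that visual cues in VR could add load. The Cognitive Load Theory section says that overload can impede learning. A cost that goes unseen is the error that matters when deciding whether to put IBVR into a curriculum.

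**Working it through.** **Inputs from the Protocol.** 64 participants allocated 1:1, so 32 per arm; two-sided alpha 0.05; Mann-Whitney for the questionnaires; planned drop-out about 10%, and 32 × 0.9 = 28.8, so about 29 per arm. The sample size is set on DOPS alone (85 ± 10 against 90 ± 10, an effect of 0.50 SD).

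**Assumptions.** The Protocol gives no planning effect or SD for load or HRV. I take true differences of 0.3, 0.5 and 0.7 SD, normal outcomes and equal SDs. For reaction time and HRV I read the Wilcoxon rank test as a between-group rank-sum test on changes, with the SD being that of the change.

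**Step 1: the plan's own figure.** The Protocol states 29 per group for 95% power, from a two-tailed Wilcoxon signed-rank test. That is a paired or one-sample test. With the rank-test efficiency 3/π = 0.955 and an effect of 0.50, it needs N = 57, and 57/2 = 28.5 rounds to 29. The stated figure is therefore matched only if a paired total is split over two groups. For two independent groups the Mann-Whitney test needs 110 per arm. The stated 95% therefore gives no assurance about any between-group comparison, including load and stress.

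**Step 2: chance of missing a true difference.** Effective size per arm n' = 0.955 × 32 = 30.56; degrees of freedom 2n' − 2 = 59.1; noncentrality = d × √(n'/2) = d × 3.909; critical t = 2.001. Power comes from the noncentral t distribution.

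| True difference | Noncentrality | Miss rate, formula | Miss rate, simulation |
|---|---|---|---|
| 0.3 SD | 1.17 | 79% | 79% to 80% |
| 0.5 SD | 1.95 | 51.5% | 52% to 53% |
| 0.7 SD | 2.74 | 23% | 24% |

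At 0.5 SD the range over methods is 48% (normal approximation) to 55% (minimum rank efficiency 0.864). With 29 per arm it is about 55% to 56%. For HRV the Protocol links stress to a fall, so the missed effect is a decrease; the two-sided power is the same.

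**Step 3: what a null result excludes.** 95% half-width = t(0.975, 62) × √(2/32) = 1.999 × 0.25 = 0.50 SD. With an observed difference of exactly zero, an increase of up to about half an SD is still compatible with the data.

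**Scope.** None of this applies to the 10-resident crossover, which has a different design and analysis.

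**The case against.** The strongest reply is that the Protocol never says a non-significant result will be read as no increase. The sentence on better performance is an anticipated contribution, not a hypothesis, endpoint or decision rule, and the stated aim is only to compare load and HRV. A reader might infer that the plan has adopted P >= 0.05 as its test of no increase. The documents do not support that; the link is inferred from how the sections fit together. Nor is non-significance the only route. A significant difference in IBVR's favour would also support the sentence, and the Protocol has reasons to hope for one: the preliminary median HRV rose from 10.13% at rest to 30.99% with an instructional IBVR video, and most earlier work is said to find that VR simulation reduces load.

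It is also fair that the nulls use equivalence loosely for no difference. The same word covers DOPS, where a 5-point gain is expected. Load scales are secondary outcomes, HRV and reaction time are listed as other outcomes, and sizing a trial on its primary outcome is normal. Margins and intervals for such outcomes can be left to an analysis plan, so their absence alone is not the fault.

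The low power is not special to load and stress either. On the planned effect DOPS itself has about 48% power at 32 per arm, which is a separate defect in the sample-size section.

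What stands is narrower. The Protocol itself fixes the equivalence wording, the difference tests and the anticipated conclusion, and its introduction already treats P = 0.303 as equivalence. A larger sample would shrink the miss rate but would not make P >= 0.05 evidence of no increase.

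**Conclusion.** The concern holds as a matter of interpretation, and the wording should be changed. Any statement that IBVR did not raise load or stress would be unsupported if it rested on a non-significant difference test. In the parallel trial such a test misses a true 0.5-SD change about 52% of the time (about 80% at 0.3 SD, 24% at 0.7 SD), and the interval is about ± 0.5 SD.

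The figures are per measure. They rest on assumed effect sizes, normal outcomes with equal SDs, complete data on 32 per arm, and a between-group rank-sum test for reaction time and HRV. They do not show that load or stress will rise, and they do not show that the trial must be run as a non-inferiority or equivalence trial.

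**What to change.** 1. Under Null Hypothesis, word the load and stress nulls as no difference between modules, and state that P >= 0.05 will not be read as equivalence or as no increase in load or stress. Carry the same wording into the crossover section.
2. Report the between-arm difference with a 95% confidence interval for CLS, TLX, reaction time and HRV. Report the CLC by component (intrinsic, extraneous, germane). Its six items include two on germane load, which the curriculum-design section aims to increase while reducing extraneous load, so the total has no single harmful direction.
3. In the anticipated contributions, word a non-significant result as: an increase of up to [upper confidence limit] was not excluded. For HRV this becomes a decrease, with the lower limit.
4. A non-inferiority margin is optional, and only if it can be fixed before the data are seen. The Protocol lists enrolment and completion (October 2020) as actual, so that may no longer be possible. Items 1 to 3 do not depend on it.

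The cost is a few sentences and one interval per measure or component, on data the trial collects anyway, with no more participants. The downside is that the message of better performance at no cost in load or stress becomes harder to claim.
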